## 3.4. Criteria for Inclusion, Exclusion and Withdrawal of subjects

### 3.4.1. Inclusion Criteria

1) Patients with histologically proven recurrent and/or metastatic NPC;

Patients with recurrent and/or metastatic NPC shall meet any of the following: 1. Recurrence after radiotherapy; 2. Metastasis

2) Patients who have failed the platinum-based therapy and received at least first-line platinum-containing chemotherapy;

3) Male or female patients: aged 18-70 y/o;

4) ECOG Performance Status score: 0-2;

5) The estimated survival is ≥ 3 months;

6) Patients not receiving chemotherapy or radiotherapy 4 weeks before the inclusion;

7) With at least one measurable lesion according to the RECIST criteria (the size measured with B-mode ultrasound, MRI or spiral CT scan is ≥ 10 mm and the measurable lesion has not received any radiotherapy);

8) Patients whose major organs function well, i.e., to meet the following requirements 1 week before the inclusion:

a. Blood routine examination:

i. Hemoglobin > 80 g/L (no blood transfusion within 14 days);

ii. Neutrophil count > 1.5 × 10^9^/L;

iii. Blood platelet count > 80 × 10^9^/L;

b. Biochemical examination:

i. Total bilirubin ≤ 1.5 × ULN (upper limit of normal);

ii. ALT or AST ≤ 2.5 × ULN (upper limit of normal);

iii. Creatinine < 2.0 times the ULN, endogenous creatinine clearance rate > 50 ml/min (Cockcroft-Gault Equation);

9) Females of child-bearing age must undergo a pregnancy test (serum or urine) 7 days before the inclusion, with a negative result and a willingness to take reliable contraceptive methods during the trial;

10) Subjects voluntarily participate in the study, sign the Informed Consent form, and are well compliant and cooperative in follow-ups.

12) Patients suffering from arterial/venous thrombosis events within 6 months before the screening, such as cerebrovascular accidents (including transient ischemic attacks), deep vein thrombosis (except for patients who had venous thrombosis caused by intravenous catheterization due to previous chemotherapy and are judged to have recovered by the investigators) and pulmonary embolism;

13) Patients with renal insufficiency: Urinary routine proteinuria > 2+ and the urinary protein quantification of 24 hours is confirmed to be > 1.0 g;

14) Patients with symptomatic brain metastasis (confirmed or suspected);

15) Patients with a history of other malignant tumors in the past 5 years, except for cured skin basal cell carcinoma, cervical carcinoma in situ and superficial bladder cancer;

16) Concomitant diseases that seriously endanger patients' safety or affect patients' completion of this study, as judged by the investigators.

### 3.4.3. Removal Criteria

Subjects who have been included but subject to any of the following circumstances should be removed from the study:

1) The subject is found to be mistakenly included in the trial because he/she did not meet the inclusion/exclusion criteria;

2) The subject fails to follow the drug dosage, administration method and course of treatment specified in this study protocol (but he/she should be observed for drug-related AEs).

### 3.4.4. Withdrawal Criteria

In case of any of the following circumstances, the investigator should discontinue the study and ask the subject to withdraw from the study. Before withdrawal, the investigator should complete the latest evaluation of all indicators, and record in detail the reason and date of the subject's withdrawal.

1) The subject voluntarily withdraws the Informed Consent form and ask to withdraw from the study;

2) The subject has disease progression with medical imaging evidence (e.g., CT, MRI examination results), or clinical progress clearly judged by the investigator (need to record the reasons to judge progress in detail);

3) The subject gets pregnant during the study;

4) The subject delays medication for over 4 weeks;

5) The subject is intolerant to drug toxicity;

6) The subject develops unexpected or unacceptable drug-related adverse reactions;

7) The subject is complicated by other diseases, and is not suitable to continue the clinical study at the investigator's judgment;

8) The subject is poorly compliant, and fails to take drugs on time and at the required dose, or fails to follow the procedures of the study;

9) Other circumstances where the investigator believes it is necessary to ask the subject to withdraw from the study.

### 3.4.5. Protection of Subjects' Rights and Interests

The investigator must state to subjects that their participation in this clinical study is voluntary, and they have the right to withdraw from the study at any stage without being discrimination or retaliation, without their medical treatment or rights or interests being affected, and they can still receive treatment in other ways after withdrawal. The investigator should also make subjects aware that their participation in the study and their personal information in the trial will be kept confidential. Subjects should also be informed of the nature, purpose, expected benefits, and possible risks and inconvenience of the clinical study, optional therapies, as well as their rights and obligations under the *Declaration of Helsinki*, and they should be given sufficient time to decide whether they are willing to participate in the study and asked to sign the Informed Consent form.

## 3.5. Concomitant Treatment

### 3.5.1. Hematology Support

Prophylactic use of colony stimulating factors (G-CSF or GM-CSF) or erythropoietin is prohibited. If a subject developed febrile neutropenia and grade 3 to 4 neutropenia after the first course of treatment after enrollment, or the investigator believes his/her life may be threatened, therapeutic use of colony stimulating factors is allowed. The subsequent courses of treatment can be given corresponding G-CSF support as the disease requires.

### 3.5.2. Treatment of Non-hematological Toxicity Symptoms

Supportive treatment such as the use of antiemetics, antibiotics, analgesics or blood products can be adopted. Oral rinse can be used as therapeutic or prophylactic treatment for stomatitis.

Non-conventional therapies (e.g., herbal medicine or acupuncture) and vitamins/minerals can be used if the investigator believes that they do not affect the outcome of the study. Patients can be given bisphosphonates for osseous metastasis during treatment. Palliative radiotherapy is allowed to irradiate a small area (must be less than 5% of the bone marrow area) if systemic treatment or local pain relief does not effectively control the painful osseous metastasis lesion. All clinical complications and AEs should be positively treated. All drugs used together with Apatinib should be recorded in the CRF in strict accordance with the GCP requirement.

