### 3.5.3. Others

Patients are not allowed to receive any other investigational therapies or any other anti-tumor therapies.

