## 3.9. Efficacy Evaluation

The efficacy is determined in strict accordance with the RECIST 1.1 criteria.

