### 3.9.2. Record Tumor Measurement Data

Target lesions should include all the organs involved, with a maximum of 5 target lesions in each organ, and the total number of all target lesions should not exceed 10. They should be measured and recorded at baseline and at the time points specified. Target lesions should be selected based on the size (lesions with the largest diameter) and suitability for repeated accurate measurability (with imaging technique or clinical methods). A primary lesion should be classified as a target lesion only if it can be accurately measured.

The longest diameter of each target lesion will be recorded. The sum of the longest diameters of all target lesions will be calculated and recorded. During the treatment, the objective response of tumors in measurable dimensions will be further clarified by referring to the sum of the longest diameters at baseline.

All non-measurable lesions and other measurable lesions not selected as target lesions should be identified as non-target lesions, and should also be recorded at baseline. Measured data of such lesions are not required in the study, but their presence and disappearance should be tracked throughout the study period.

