### 3.9.3. Efficacy Evaluation Indicators

#### 3.9.3.1. Primary Efficacy Indicators

Objective response rate (ORR): The proportion of patients whose tumors shrink to a certain size and maintain such size for a certain period of time, including patients with complete response (CR) and partial response (PR).

The RECIST 1.1 criteria for solid tumor response will be used to evaluate the objective response of tumors. Subjects should have measurable tumor lesions at baseline, and the efficacy evaluation criteria will be divided into CR, PR, SD and progressive disease (PD) according to the RECIST 1.1 criteria.

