#### 3.9.3.2. Secondary Efficacy Indicators

Disease control rate (DCR): The proportion of patients with response and stable disease (SD) after treatment, including patients with CR, PR and SD.

Duration of Response (DoR): Duration from the first PR to PD.

Progression-free survival (PFS): Duration from the date of inclusion of the patient to the date of any recorded tumor progression or death from whatever cause. Analysis of this indicator includes tumor evaluation results during treatment and the follow-up period. If a patient has several indicators that can be judged as PD, the indicator that appears first should be used for PFS analysis. Relapse, new lesion or death will be considered as the outcome of the study. If the patient is receiving other systemic anti-tumor treatment or treatments for the observed target lesions, he/she should also be regarded as PD. For a patient who has no PD or dies when the study ends, the last time he/she does not have PD will be taken as the censored data.

Overall survival (OS): Duration from the date of inclusion to the date of death from whatever cause. For a subject still alive at the last follow-up, his/her OS is counted as data censored at the last follow-up time. OS for data censoring is defined as the duration from the inclusion dateto the censoring date.

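### Treatment of a target lesion counts as PD for PFS but not for ORR, DCR or DoR, so a target bone lesion irradiated under 3.5.2 can be PD for PFS and PR for the primary endpoint

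*Protocol*

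**What the plan says.** Five parts of the protocol bear on this.

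- **3.5.2, concomitant treatment.** "Palliative radiotherapy is allowed to irradiate a small area (must be less than 5% of the bone marrow area". This applies to a painful bone metastasis that systemic treatment or local pain relief has not controlled. Nothing limits it to non-target lesions.
- **3.5.3, the next section.** "Patients are not allowed to receive any other investigational therapies or any other anti-tumor therapies". Radiotherapy is not named, and there is no cross-reference to 3.5.2.
- **3.9.3.2, inside the PFS paragraph.** "If the patient is receiving other systemic anti-tumor treatment or treatments for the observed target lesions, he/she should also be regarded as PD". The DCR and DoR definitions in the same section do not repeat this. DoR runs from first PR to PD.
- **3.9.3.1, the primary endpoint.** ORR is "The proportion of patients whose tumors shrink to a certain size and maintain such size for a certain period of time", made up of CR and PR. It says nothing about a lesion treated locally after baseline.
- **3.4.1 and 3.9.2, the lesions.** At entry the protocol requires that "the measurable lesion has not received any radiotherapy". "Target lesions should include all the organs involved", so a measurable bone lesion can be a target. For non-target lesions, "Measured data of such lesions are not required in the study, but their presence and disappearance should be tracked throughout the study period".

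**The concern.** The protocol accepts that response in a lesion treated by other means is not evidence about the study drugs. It bars irradiated measurable lesions at entry. It treats therapy to a target lesion as PD for PFS. In 3.8.3 it ends off-treatment tumour evaluations when other anti-tumour therapy starts. The on-treatment assessment of ORR, where the principle matters most, has no such rule.

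Two consequences follow. The same patient can be progressed for a secondary endpoint and a responder for the primary one. And in a single-arm trial judged against a fixed 24.2%, any radiotherapy effect counted as response biases ORR upwards with no control arm to offset it.

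**Working it through.** **1. The definitions applied to one patient.** The dates are illustrative. The deemed PD date is taken as the start of radiotherapy, because 3.9.3.2 gives no date rule. Cycles last 3 weeks and imaging is every two cycles, so scans fall near weeks 6 and 12. Suppose a target bone lesion is irradiated at week 5 and the sum of target diameters first meets PR at week 12.

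| Endpoint | Rule in the protocol | Result |
| --- | --- | --- |
| PFS | treatment of a target lesion is PD (3.9.3.2) | event at week 5 |
| ORR | CR + PR, no treatment rule (3.9.3.1) | responder at week 12 |
| DCR | CR + PR + SD, no treatment rule | controlled |
| DoR | first PR to PD | 5 − 12 = −7 weeks if the deemed PD is used; otherwise it runs to a later PD that PFS ignores |

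The withdrawal criteria in 3.4.4 list progression on imaging and progression clearly judged by the investigator. They do not list this deemed PD, so the patient can remain on study and have the week 12 scan.

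**2. How wide the route is.** An extra PR needs a bone lesion that is measurable, chosen as a target, painful, irradiated, and large enough to move a sum of up to 10 target diameters to PR. Non-target lesions are not measured, so their shrinkage cannot produce a PR. Disappearance of an irradiated non-target lesion could be counted towards CR. A patient already PR on the target lesions is a responder either way, so this second route bears mainly on the CR count.

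**3. The plan's sample size.** Inputs from 3.3: p0 = 0.242, p1 = 0.392, one-sided alpha 0.05, power 0.80, first stage n1 = 31 with a stop at 7 or fewer responses, 10% drop-out, N = 64. For a two-stage design,

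P(success | p) = Σ over x = 8 to 31 of b(x; 31, p) × P(Bin(n − 31, p) > r − x).

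An exact search gives the minimax design n1 = 31, r1 = 7, n = 58, r = 19, with alpha 0.0495 and power 0.8002. Adding 10%, 58 × 1.1 = 63.8, or 64 as stated. The first stage also matches. The final boundary (success at 20 or more of 58) is inferred; the protocol does not print it.

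**4. What one such responder does.**
- N = 64: 1/64 = 1.6 points.
- n = 58: 1/58 = 1.7 points. 19/58 = 32.8% fails and 20/58 = 34.5% succeeds under the inferred boundary.
- n1 = 31: 1/31 = 3.2 points. 7/31 stops the trial and 8/31 continues it.

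**5. Sensitivity of the type I error (an assumption, not an estimate).** Let a fraction d of true non-responders be scored as responders because of radiotherapy. Then p = 0.242 + d × (1 − 0.242). In 58 patients, expected non-responders under p0 are 58 × 0.758 = 43.96.

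| d | p | Expected false responders (43.96 × d) | Type I error, 31/58 design |
| --- | --- | --- | --- |
| 0 | 0.2420 | 0 | 0.0495 |
| 1% | 0.2496 | 0.44 | 0.066 |
| 2% | 0.2572 | 0.88 | 0.085 |
| 3% | 0.2647 | 1.32 | 0.108 |
| 5% | 0.2799 | 2.20 | 0.166 |

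The protocol gives neither the frequency of bone target lesions nor that of on-study radiotherapy, so no row can be preferred.

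**The case against.** **The response criteria and the SAP may settle it.** Section 3.9 says "The efficacy is determined in strict accordance with the RECIST 1.1 criteria", and response derivation is often left to an SAP or imaging charter. But the protocol does not leave this subject alone. It writes its own rule on treated lesions and places it in one endpoint definition. The resulting conflict between two protocol definitions does not depend on what an SAP adds.

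**PD is PD.** PD is one of the four response categories in 3.9.3.1, so a patient regarded as PD at week 5 might be taken as PD for ORR too. That reading is reasonable and is the one the fix adopts, but the text does not say it.

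**Independent review.** Section 3.11.5 has an independent imaging committee confirm every CR, PR, SD and PD. It is a real check on measurement, but it has no stated rule for irradiated lesions.

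**Stronger readings that the documents do not support.**
- A reader might infer that 3.5.3 bans what 3.5.2 allows. The ban is on any other therapy and directly follows the specific permission, so it reads naturally as other than the above. The wording is unclear rather than a firm contradiction.
- A reader might infer that all palliative bone radiotherapy is PD for PFS. The local-treatment part of the rule covers target lesions only.
- A reader might infer that irradiating a worsening non-target lesion hides progression and inflates PFS and DCR. The trigger in 3.5.2 is uncontrolled pain, not growth. Scheduled imaging continues, 3.8.2 allows extra imaging for suspected progression, and 3.4.4 recognises clinical progression.
- A reader might assume a radiotherapy rate and read it as a count of false responders. Irradiated patients are not false responders; few of them would meet every condition in step 2 of the working.

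**Conclusion.** The point holds in a limited form. The protocol permits on-study radiotherapy that may reach a target lesion and calls treatment of a target lesion PD for PFS only. The same patient can therefore be PD for PFS and PR for the primary ORR, with a DoR that starts after the PD date. Any resulting error in ORR is upwards.

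The size per patient is clear: 1.6 points at N = 64, and enough to cross either decision line if the count stands at 7/31 or 19/58. The second line rests on the reconstructed minimax boundary. The expected number of such patients is unknown, may well be small, and cannot be computed from the protocol. This is a cheap improvement that makes the endpoints consistent. It does not show that ORR will be materially biased, and the stated sample size is unaffected.

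**What to change.** - State in 3.9.3 that the rule on other systemic treatment and treatment of target lesions governs ORR, DCR, DoR and PFS alike. Best overall response then uses only assessments made before any treatment of a target lesion or other anti-tumour therapy. A patient so treated before any response stays in the denominator as a non-responder. A response recorded earlier stands, and its DoR ends at the deemed PD date, which the rule should define.
- State that disappearance of an irradiated non-target lesion does not count towards CR.
- Flag on-study radiotherapy in the response dataset, with lesion and date.
- The sponsor should reconcile 3.5.2 with 3.5.3. No view is taken here on whether radiotherapy should be permitted or on when to scan.

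The cost is protocol wording and one dataset flag. The downside is that ORR may be slightly lower.

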### 3.5.3. Others

Patients are not allowed to receive any other investigational therapies or any other anti-tumor therapies.

## 3.6. Dose Delay and Adjustment

The dose of Apatinib and Capecitabine can be reduced in the study. For Apatinib, the reduction levels are from 500 mg once daily to 500 mg and 250 mg on alternate days, to 250 mg once daily. For capecitabine, 25% and 50% dose reduction will be given. If the subject is still intolerant to the toxicity after the dose is reduced, he/she should be excluded from the study. During the entire study period, the dose is allowed to be reduced at most twice, and shall not be increased.

The drug can only be suspended or its dose can only be reduced when a subject has grade III or worse adverse events or grade II intolerable toxicity assessed by the clinicians. Controllable nausea, vomiting and fever (below 38°C) with a clear cause can be actively handled and treated symptomatically without suspending the drug or reducing its dose. The dose and suspension of the drug should be stated in the final study report.

To ensure the drug intensity to the subjects in the trial, the time of each drug suspension and the cumulative time of suspension during each administration cycle shall not be over 14 days, and the suspension shall not exceed two times during each cycle. If the drug discontinuation time or the number of suspensions exceeds the requirement, the subject will withdraw from the study, but his/her tumor shall still be evaluated following the study procedure.

## 3.7. Symptomatic Treatment of Common Adverse Reactions of Apatinib and Capecitabine

### 3.7.1. Hypertension

Tumor patients with hypertension should use anti-hypertension drugs appropriately to control their blood pressure before receiving anti-VEGF/VEGFR drugs, while tumor patients with poorly controlled hypertension should use anti-VEGF/VEGFR drugs with caution. Early blood pressure control is important for protecting the renal function. The elevated blood pressure in those patients during treatment will drop after the discontinuity of drug, and generally no further treatment is needed. However, patients with significantly elevated blood pressure (blood pressure ≥ 140/100 mmHg) and/or corresponding symptoms should be given antihypertensive treatment. Current routine combinations of drugs for hypertension are the combined use of ACEIs or ARBs with diuretics, calcium channel blockers with β-receptor blockers, ACEIs with calcium channel blockers, diuretics with β-receptor blockers, and α-receptor blockers with β-receptor blockers. The common antihypertension drugs, including Diuretics, β-receptor blockers, Calcium channel blockers, Angiotensin converting enzyme inhibitors, Angiotensin II receptor blockers should be considered in clinical practice.

**Grading criteria and prevention and treatment recommendations for hypertension (NCI-CTCAE 4.0)**

| Grading | Definition | Prevention and treatment recommendations |
| --- | --- | --- |
| Grade 1 | Systolic pressure of 120 to 139 mmHg  Or diastolic pressure of 80 to 89 mmHg | Closely monitor the blood pressure; limit salt intake, and quit smoking and alcohol;  Continue to use Apatinib without dose adjustment |
| Grade 2 | Systolic pressure of 140 to 159 mmHg  Or diastolic pressure of 90 to 99 mmHg | Closely monitor the blood pressure; continue to use Apatinib without dose adjustment in normal cases; Should take anti-hypertension drugs and should not discontinue anti-hypertension drugs at will |
| Grade 3 | Systolic pressure ≥ 160 mmHg Or diastolic pressure ≥ 100 mmHg | Suspend Apatinib; Single-agent poorly controlled hypertension, combined medication should be considered;; consult and receive treatment from cardiovascular specialists; closely monitor the blood pressure; reduce the dose of Apatinib and continue to use it if the blood pressure is well controlled |
| Grade 4 | Life-threatening (malignant hypertension or persistent nerve injury, hypertensive crises) | Discontinue Apatinib immediately and permanently; consult cardiovascular specialists for active treatment of hypertension, and closely monitor the blood pressure and other vital signs |
| Grade 5 | Death |  |

Note: Patients with hypertensive crisis should discontinue Apatinib permanently and withdraw from this clinical study.

### 3.7.2. Proteinuria

For all cancer patients treated with anti-VEGF/VEGFR drugs, urine protein must be closely monitored during treatment, especially during the first 6 weeks of treatment. It is recommended to check urine routine and/or 24-hour urine protein quantification every 2 weeks for the first 2 months, and then check every 4 weeks. Patients with positive results of urine protein should have creatinine test on a regular basis to assess renal function. Patients with urine protein +++ or 24-hour urine protein > 3.5 g should consult with a nephrologist and consider stopping the drug appropriately. Patients with stage 3 chronic kidney disease or above should take apatinib with caution. As ACET and ARB drugs may reduce the pressure in the kidney tubules, thus reducing proteinuria, they can be taken as appropriate.

